## Abstract

**Aims:**

Heart failure (HF) is a growing problem in society with an ageing population and many patients with heart failure are affected by renal dysfunction. The RENAL-HF project aims to develop predictive risk models to support personalized renal function monitoring and treatment in patients with HF in primary care.

**Methods and results:**

This study will use electronic health records from the Clinical Practice Research Datalink (CPRD) database for patients who were diagnosed with HF. We will develop three prediction models—Mixed-effects model, Growth mixture model, and recurrent neural network-long short-term memory model to predict future worsening renal function, including events that lead to hospitalization, and death. Using an internal-external validation approach based on geographic region, we will choose the top-performing model using various metrics to evaluate the predictive performance.

**Conclusion:**

This protocol provides a detailed description of the methods used for developing and validating prognostic models for personalized renal function monitoring in people with HF in primary care.

**Protocol registration:**

The study and use of CPRD data were approved by the Independent Scientific Advisory Committee for Clinical Practice Research Datalink research (**Protocol Number: 22_001794).**

## Introduction

Approximately 15 million people in the Europe live with heart failure (HF), most of whom also have renal problems.^1^ In the UK as well as in other countries, most of these patients are managed in primary care. Modern therapy for people with HF comprises a combination of drugs, with dose titration being important to optimize control, and therefore improve prognosis. Sub-optimal treatment regimens and doses can lead to a progression of HF symptoms, and in turn worsen renal function. Conversely, over-treatment can also impair renal function. Either can lead to hospitalization and increases the risk of death.

There are no clear clinical guidelines on how renal function monitoring should be carried out in patients with HF. Even if population-based guidelines were available, they will be variably followed and may also be wasteful in terms of unnecessary testing for patients, increasing the burden on healthcare services and impairing the quality of life of patients. Hence, there is a need for tools that can inform primary care clinicians in the monitoring of renal function and guide treatment decisions.

The RENAL-HF project aims to develop an evidence-based system to support personalized renal function monitoring and treatment in patients with HF. Rooted in prediction technology, this system models the dynamic trajectory of renal function (serum creatinine) to predict the risk of worsening renal function (WRF) over a rolling 12-month horizon. Clinical prediction models (CPMs) are becoming increasingly important in modern clinical practice, informing healthcare professionals, patients, and families about the risks of outcomes, facilitating (shared) healthcare decision-making and improving health outcomes.^2^

There are several validated CPMs for the prediction of the onset and progression of chronic kidney disease (CKD) and for stratification of risk in patients with HF. These models focus on outcomes such as risk of admission and readmission, renal complications, and mortality.^3–10^ However, most of these models focus solely on static risk factors and do not directly deal with the dynamic changes in renal function over time. It is worth noting that comparative studies such as Christodoulou *et al*. showed the abilities of machine learning (ML) models and traditional statistical prediction methods in the clinical field.^11^ This study builds on this evidence base by explicitly comparing methods for the personalized monitoring of renal function in HF patients using statistical and ML frameworks.^12–16^

In this study, we provide a detailed scientific protocol for developing, validating, and comparing CPMs. This protocol directly compares three modelling strategies: mixed effects and growth mixture models (representing statistical approaches) and the recurrent neural network-long short-term memory (RNN-LSTM) model (an ML approach), applied to longitudinal electronic health records data from HF patients for the prediction of WRF over a 12-month horizon.

These models will be assessed using various evaluation metrics such as model performance, sustainability, interpretability, parsimony, novelty, implementation, and fairness. These metrics will help to identify the most suitable model to be used in a future clinical trial. This article describes the study protocol in three main stages: the development of WRF predictive models, the validation process of the models, and the selection of the final model for a clinical trial.

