### Prediction models

To predict serum creatinine trends, we will perform and compare three different modelling strategies. Modelling a continuous trajectory allows us to capture the rate of decline and dynamically recalculate the risk of WRF in relation to the change in baseline patient. This approach offers greater clinical utility than binary classification alone.

**Mixed-effects model**: The longitudinal component is based on a linear mixed-effects regression model. Variable selection is done with the least-absorption and selection operator (LASSO) to avoid overfitting by penalizing regression coefficients.
**Growth mixture model:** GMM is used to identify latent subgroups (classes) of a population that follow different growth trajectories. To mitigate overfitting in the GMM, the optimal number of latent classes (K) will be determined using the Bayesian information criterion and Akaike information criterion, with a minimum class size constraint enforced to ensure generalizability.
**RNN-LSTM:** Deep learning model using LSTM will be developed to handle complex nonlinear time dependencies. The model architecture consists of two LSTM layers (64 units each) with a dense output layer. To address the specific data requirements of neural nets, continuous variables (e.g. creatinine, urea) will be log transformed or standardized to ensure effective optimization, while clinical scales will be used in statistical models. To meet the specific data requirements of ML models, the continuous variable log transformation or standardization will be performed. Overfitting in RNN-LSTM is mitigated by early stopping, where training is stopped when the validation loss does not improve after a certain number of epochs (patience), in combination with drop-out regularization layers.

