### Dynamic renal test recommendation system

Dynamic renal test recommendation system module aims to dynamically recommend renal tests based on inputs from the main model. The system proposes time to renal blood test using NICE (National Institute for Health and Care Excellence) guideline as backbone. The proof-of-concept R code is provided in Supplementary File  *S4*. The RNN-LSTM model (Main model) would provide estimations of future serum creatine levels based on historic data of a patient. The NICE guideline offers thresholds and requirement for assessing renal function and identifying WRF. We will adopt the RNN-LSTM prediction model's output to inform the NICE guideline recommendations.

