#### Clinical utility

To assess the practical value of the models, we will perform decision curve analysis. This method calculates the ‘Net Benefit’ of using the model to guide monitoring decisions across a range of threshold probabilities, comparing it against default strategies (e.g. monitoring everyone or no one). We will use methods described in previous research studies to calculate net benefits.^41,42^

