## Discussion

This protocol outlines our planned study for creating and validating a prediction model for future serum creatinine trends in people with HF. Conventional renal monitoring strategies utilizing static serum creatinine or estimated GFR values often fail to capture the dynamic nature of renal function in HF patients. Our framework provides a clear guideline for developing and validating both statistical and ML algorithms for clinical implementation.

Our protocol addresses several challenges with respect to predictive model development. Serum creatinine is influenced by factors such as muscle mass and hydration. Although our model development process will focus on a specific cohort (UK), external validation in diverse populations will be required to confirm generalizability. Looking ahead, prospective studies will be needed to determine whether model-based interventions can reduce adverse effects on the kidney, optimize HF therapy titration, and improve overall clinical outcomes. This will be tested in a planned randomized controlled trial in the future.

Our protocol sets out a clear, step-by-step methodology for developing and validating a predictive model for monitoring renal function in HF patients. The protocol describes standardized data collection, obvious inclusion/exclusion criteria, rigorous preprocessing (including dealing with missing data), and the development of both statistical and ML algorithms. We also outline plans for internal and external validation across diverse populations and describe how the final model could be integrated with electronic health platforms to enable real-time decision support. This comprehensive methodological framework not only aims to develop an effective forecasting tool but also sets a reproducible standard for high-quality research in renal function monitoring in HF.

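### The three dynamic models are ranked against each other with no simple static reference for worsening renal function, so the study cannot show that any of them adds to current creatinine

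*Protocol article*

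**What the plan says.** The comparison set is given twice. The Introduction says "This protocol directly compares three modelling strategies", and the Prediction models section repeats it: "To predict serum creatinine trends, we will perform and compare three different modelling strategies". The Abstract says the top performer will be chosen, and the Introduction says the chosen model is meant for a later trial.

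The yardsticks are RMSPE for predicted creatinine, calibration, the C-statistic for WRF, and net benefit in a decision curve. The Clinical utility section describes the last as "comparing it against default strategies (e.g. monitoring everyone or no one". The Model selection section quantifies its accuracy criterion by RMSPE.

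The rationale is comparative. The Introduction faults most existing prediction models for relying on static risk factors, and the Discussion says: "Conventional renal monitoring strategies utilizing static serum creatinine or estimated GFR values often fail".

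Last creatinine enters the plan only as a time-varying input to the candidates (Predictors section). The Cox, landmark and joint latent class models under Outcome predictions address secondary outcomes or other model forms. They are not WRF benchmarks.

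**The concern.** A ranking of three dynamic models answers which of them is best. It does not answer whether any of them is better than a clinician reading the current creatinine, which is the claim that motivates the work. RMSPE on creatinine has no natural zero point: whether a value is good depends on what a trivial forecast would achieve in the same patients. The C-statistic and net benefit have absolute anchors, but those anchors correspond to having no information, not to knowing the current value.

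At stake is the model's entry to a trial. If most of the winner's performance comes from current creatinine, age and sex, the planned output would not reveal it. The consensus panel would then weigh interpretability, simplicity and sustainability without knowing what the added complexity buys.

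**Working it through.** The plan states no figure on this point, so there is none to reproduce. The check has four steps.

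**1. What is compared with what.**

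| Element | What the article states | Static reference named? |
|---|---|---|
| Candidates | Mixed-effects, growth mixture, LSTM | No |
| RMSPE | Predicted against observed creatinine | No |
| C-statistic, calibration | For WRF, per candidate | No |
| Decision curve | Default strategies, two given as examples | No |
| Selection | Top performer or most suitable, by consensus | No |

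**2. Why RMSPE needs a reference (illustration, assumed correlation).** Let successive values have equal mean and SD and correlation r. The article gives no r; 0.80 to 0.95 is assumed.

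- Carry-forward: RMSPE = SD × √(2(1 − r)).
- Best one-lag linear predictor: RMSPE = SD × √(1 − r²).
- Ratio: √(2/(1 + r)).

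| r | Carry-forward (SD) | One-lag optimum (SD) | Ratio |
|---|---|---|---|
| 0.80 | 0.632 | 0.600 | 1.054 |
| 0.90 | 0.447 | 0.436 | 1.026 |
| 0.95 | 0.316 | 0.312 | 1.013 |

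A rule that learns nothing comes within 1.3% to 5.4% of the one-lag optimum. Neither rule is a candidate, so this does not estimate what the three models gain. It shows only that an RMSPE cannot be read without its reference.

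**3. Why current creatinine may itself predict WRF.** The Outcomes section defines WRF as either a 30% rise or a rise of 26.5 µmol/L. The two criteria coincide at 26.5/0.30 = 88.3 µmol/L. Above that level the absolute criterion is easier to meet: at twice the level, 26.5/176.7 = 15%. A patient with high current creatinine therefore needs a smaller relative rise. Unless relative variability falls equally fast with level, the current value alone will discriminate to some extent. How far is unknown, which is why it should be measured.

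**4. How high the all-or-none bar is (illustration, assumed C-statistics).** Prevalence is 0.25, the approximate value in the Sample size section. At threshold p,

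NB = 0.25 × TPR − 0.75 × FPR × p/(1 − p).

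For a calibrated binormal score, d = √2 × Φ⁻¹(C). Monitoring everyone gives NB = 0.25 − 0.75 × p/(1 − p): 0.167 at 10%, 0.0625 at 20% and 0 at 25%. At p = 0.25 the score's NB reduces to 0.25 × (2Φ(d/2) − 1). With C = 0.55, d = 0.178 and NB = 0.25 × 0.071 = 0.018.

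Gain over the better of the two defaults:

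| C | p = 10% | p = 20% | p = 25% |
|---|---|---|---|
| 0.55 | 0.000 | 0.001 | 0.018 |
| 0.60 | 0.000 | 0.009 | 0.036 |
| 0.65 | 0.001 | 0.022 | 0.054 |
| 0.70 | 0.003 | 0.037 | 0.072 |
| 0.75 | 0.008 | 0.052 | 0.092 |

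Near the prevalence even a weak calibrated score beats both defaults; at 10% the bar is much harder to clear. Passing it shows that a score carries information, not that the information goes beyond current creatinine.

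**The case against.** Several stronger readings are tempting, and the article does not support them.

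- **That the decision curve is confined to two defaults.** The wording is "comparing it against default strategies (e.g. monitoring everyone or no one", and the abbreviation leaves the list open. All that can be said is that no static strategy is named.
- **That the plan calls existing guideline schedules wasteful and fails to test this.** The remark "may also be wasteful in terms of unnecessary testing for patients" concerns population guidelines supposing they existed, directly after a statement that no clear ones exist for renal monitoring in heart failure. The recommendation module does take the NICE "guideline as backbone", which sits awkwardly with that statement. But the module is not one of the three compared strategies, and a testing schedule would have to be turned into a test or no-test rule before it could enter a decision curve. A guideline comparator is optional.
- **That a model merely repeating the last value would pass unnoticed.** It would not. WRF is a rise, and a literal carry-forward forecast predicts none. It has a C-statistic of 0.5 and coincides with monitoring no one. The planned WRF metrics would expose it, however low its RMSPE.
- **That the illustrations show the candidates add almost nothing.** They do not. The candidates use full history, laboratory tests and medication, and the correlations and C-statistics are assumed.

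Two further points carry weight. Supplementary Files S3 (metrics) and S5 (selection criteria) are not shown and could contain a benchmark. The Discussion also leaves clinical benefit to prospective studies and a randomised trial. But the article is explicit about its comparison set and names no reference, and a trial would expose a model of no added value only after that model had been selected.

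**Conclusion.** The concern holds in a limited form. As described, the study can rank three dynamic models and report absolute discrimination and calibration for each. It cannot quantify what any of them adds to current creatinine, although that is the premise on which it is justified. No planned analysis is invalid, and a poor model would not necessarily be selected. The size of the gap cannot be derived from the article: the RMSPE ratios of 1.013 to 1.054 and the net-benefit gains rest on assumed values and serve only as illustration. The conclusion itself rests on the stated comparison set and on no static reference being set out in the supplements. It merits a change because the missing comparison is cheap and bears directly on the choice of model.

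**What to change.** Score two references in the same nine leave-one-region-out folds and the 20% hold-out described under Validation:

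1. Last creatinine carried forward, as the reference for RMSPE.
2. A static WRF risk model on current creatinine, age and sex, for the C-statistic, calibration and net benefit, with its curve added to the decision curve.

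Report each candidate's difference from these references, pooled by the planned random-effects meta-analysis with 95% confidence and prediction intervals. Give the differences to the consensus panel as part of the accuracy criterion. A fixed minimum gain for going forward is not required, but the references should be set down before results are seen.

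The cost is a little extra analysis on variables already in the dataset. The candidates may also look less favourable than they would without a reference.

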## Methods

The study is structured as follows: model development (conventional statistical and deep learning models), model validation (internal and external), and model comparison using consensus selection technique. The overview diagram (*Figure 1*) shows the data flow and the analysis steps, including which datasets are used in each step. This protocol complies with the relevant parts of the TRIPOD-AI statement on reporting of clinical predictive modelling studies using artificial intelligence.^17,18^ The completed TRIPOD-AI checklist is included in Supplementary File  *S1*.

**Figure 1 ztag055-F1:**
[figure not shown]
Flow chart describing overall view of study design.

### Data source

Using a retrospective cohort study design, we will use EHRs of HF patients to develop and validate predictive models of future renal function based on clinical and patient factors. The CPRD holds pseudonymized patient data from GP practices across the UK. In this study, we will be using records from the CPRD Aurum database for prediction model development.^19^ All predictor variables shall be derived from data collected routinely in the primary care setting. Outcome variables for hospitalization and mortality will be determined through the linkage to secondary care using hospital episode statistics and mortality data from the Office for National Statistics. In addition, the data will consist of socioeconomic status at the patient and practice-level (as a covariate and potentially for stratification) using the Index of Multiple Deprivation (IMD). In the CPRD databases, clinical diagnoses, medication, and laboratory test results are coded using a combination of Read v2, SNOMED CT, and local EMIS codes.

### Participants

The study population will consist of all patients with their first ever recorded diagnosis of HF between 1 January 2005 to 1 March 2022. We chose to use data after 2005 as the Quality and Outcomes Framework (QOF) was introduced in UK general practices in 2004 and resulted in improved recording in medical records of long-term conditions in primary care. All registered patients with a first Read v2 or SNOMED CT code for HF during the study period will be included in the study population. The clinical code lists will be made available in the GitHub repository: https://github.com/alxv/Renal-HF.

There will be no restrictions to location in terms of the population sampled. A patient’s follow-up will commence on their index (onset of HF) date and terminate on either the last date of data collection (at the practice-level), the date that they transferred out of the practice, their date of death, or the end of the study, whichever happens first. Patients will be excluded from the study if they have had a history of renal replacement therapy (dialysis, filtration, or transplant) prior to their HF diagnosis. Patients who die or are lost to follow-up before the first valid serum creatinine (t_0_) is measured are excluded from longitudinal analysis as it is not possible to determine baseline renal function. A flow diagram of criteria for inclusion/exclusion is presented in *Figure 2*.

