### Outcomes

The primary endpoint of the study will be worsening of renal function. Early detection or prediction of WRF provides an opportunity for intervention to prevent progression to renal failure and acute kidney injury (AKI) and potentially prevent hospitalization and death. Serum creatinine was selected as the primary biomarker for modelling. While a retrospective glomerular filtration rate (eGFR) recalculation using a single formula (CKD-EPI 2021) was a way of standardizing the historical data, we decided on raw serum creatinine. This approach avoids any bias. The raw serum creatinine allows an ML model to learn the effect of age and gender on renal trajectories directly from raw data rather than being constrained by fixed eGFR coefficients. In addition, a 12-month prediction period has been chosen to align with routine chronic disease monitoring intervals in primary care, thereby bridging the gap between acute injury (AKI) and long-term disease progression. Therefore, WRF is defined by primary care data if any of the following occur within 12 months: (i) 30% increase in serum creatinine or (ii) 26.5 µmol/L increase in serum creatinine.

Secondary outcomes will include hospitalization for AKI, major adverse cardiovascular events (MACE) and all-cause mortality. These outcomes are included specifically to consider competing risks and to recognize that patients with HF may experience cardiovascular events or death before renal monitoring.

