### Predictors

Data shall be presented in longitudinal panel data format. Although cohort eligibility is determined at the date of diagnosis of HF (index date), the longitudinal model trajectory is based on the first available serum creatinine (*t*_0_) measurement in each patient. If there is a gap between the index date and the first creatinine measurement, the static baseline covariates are shifted to *t*_0_. The longitudinal data will contain demographic information, lifestyle factors, co-morbidities and medication use associated with HF, renal decline, and mortality following a review of the literature on HF and renal function monitoring.^20–26^ The major factors for code list preparation are provided in *Table 1*. A full list of definitions for the planned predictor variables is provided (along with definitions of units of measurement, categories, and acceptable value ranges) in Supplementary File  *S2*. The code lists used to extract the relevant data and define the candidate predictors will be developed, curated, and validated by clinical experts within the RENAL-HF project team. All code lists will be made available in the GitHub repository: https://github.com/alxv/Renal-HF. The models will use two categories of predictors. Static predictors are baseline demographics (age, sex, ethnicity, deprivation index) and comorbidities observed at the index date. Dynamic predictors will be time-varying variables updated at each measurement point, including serum creatinine, other longitudinal laboratory tests (potassium, sodium, urea) and the status of active medicinal products. All models utilize data available up to the moment of prediction (*t*) to forecast outcomes at *t* + 1. Future data are never used for model development at time t.

**Table 1 ztag055-T1:** Major factors for code list preparation

Description	Factors
**Cardiovascular**	Blood pressure, hypertension, smoking status, atrial fibrillation, and ischaemic heart disease
**Renal**	Chronic kidney disease status, history of AKI, renovascular disease, dialysis, nephrectomy, proteinuria, nephritis, and anaemia
**Comorbidities**	Chronic liver disease, diabetes, systemic lupus erythematosus, and peripheral vascular disease
**Lab tests**	Haemoglobin, potassium, albumin, sodium, mean corpuscular volume, and urea
**Medication**	Non-steroidal anti-inflammatory drugs, drugs acting on the angiotensin system, specific antimicrobials, and immunosuppressants

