### Statistical modelling

The longitudinal component will consist of a linear mixed-effects regression model for the repeated measures of serum creatinine (at the patient level). To select variables for inclusion in the longitudinal sub model, we will use the LASSO proposed by Tibshirani (1996) which is based on penalized regression and uses an *L*_1_-penalty on the regression coefficients.^32^ Selection will be undertaken using a Gaussian link function in the R package glmmLasso which combines gradient ascent optimization with the Fisher scoring algorithm^33^. The mixed effects model (incorporating those variables selected via the LASSO) will be estimated using the R package nlme—as this provides the requisite outputs to be applied as arguments in the subsequent joint modelling phase. A GMM is a type of finite mixture model that assumes different subgroups (classes) in the population follow different growth trajectories. It combines features of growth curve modelling and mixture modelling. For a GMM, we assume there are *K* latent classes in the population, and each class *k* has its own growth model with distinct parameters. Within each class *k*, the model for the serum creatinine response variable is as follows:

$$y_{ij}=x_{ij}\beta_{k}+z_{ij}u_{ki}+\epsilon_{kij}$$

where

$x_{ij}$
 and $z_{ij}$ are as defined previously.

$\beta_{k}$
 is the column vector of fixed-effects coefficients for class *k*.

$u_{ki}$
 is the column vector of random effects for the *i*th patient in class *k*.

$\epsilon_{kij}∼N(0,\sigma_{k}^{2})$
 is the residual error for the *i*th patient at the *j*th measurement point in class *k*.

We will employ a joint modelling framework to link the longitudinal serum creatinine trajectory to the time to event outcome. The longitudinal sub-models (mixed-effects model or GMM) will characterize the renal trajectory. The survival sub-model will account for the informative censoring caused by competing risks such as death and MACE.

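### Starting renal replacement therapy after the HF diagnosis does not end follow-up, so creatinine values driven by dialysis or transplant are modelled and scored as native renal function

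*Protocol article*

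**What the plan says.** All of this is in the Methods of the protocol article.

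- **Exclusion (Participants).** Patients are removed for a "history of renal replacement therapy (dialysis, filtration, or transplant) prior to their HF diagnosis". The exclusion is tied to the date of diagnosis.
- **End of follow-up (Participants).** Follow-up stops at the practice's last data collection or "the date that they transferred out of the practice, their date of death, or the end of the study, whichever happens first". The list is closed and contains no RRT event.
- **Start of the modelled series (Predictors).** Eligibility is fixed at diagnosis, but "the longitudinal model trajectory is based on the first available serum creatinine" (t0), which can be later.
- **Primary endpoint (Outcomes).** WRF is either of two creatinine rises within 12 months: "i) 30% increase in serum creatinine or (ii) 26.5 µmol/L increase in serum creatinine". RRT is not a component.
- **Other outcomes (Outcomes).** "Secondary outcomes will include hospitalization for AKI, major adverse cardiovascular events (MACE) and all-cause mortality". RRT is not among them.
- **Joint model (Statistical modelling).** "The survival sub-model will account for the informative censoring caused by competing risks such as death and MACE". RRT is not named.
- **Table 1 (Predictors).** The renal code-list factors are "Chronic kidney disease status, history of AKI, renovascular disease, dialysis, nephrectomy, proteinuria, nephritis, and anaemia". Dialysis appears; transplant does not.

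**The concern.** After dialysis or transplant, serum creatinine reflects the treatment as well as the patient's own kidneys. A fall after transplant looks like recovery, and variation around dialysis sessions can look like deterioration. The plan keeps such patients out when RRT came before the diagnosis but keeps their values when RRT came afterwards, and the text shown has no rule for handling those values.

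Three things are exposed. The first is the series to which all three models are fitted. The second is the WRF label, which is computed from creatinine alone. The third is RMSPE, which squares errors and so gives a few extreme records a large weight. There is also a mismatch of purpose. The Outcomes section says prediction is meant to allow intervention before renal failure, and windows after RRT start lie outside that use.

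**Working it through.** The plan states no figure on this point, so there is none to reproduce. The check has three steps.

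**1. Does any other section remove post-RRT values?**

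- WRF and the secondary outcomes do not mention RRT.
- The competing risks in the joint model are given as examples, so RRT could be meant. Even so, a competing-event label alone would not take later creatinine values out of the longitudinal series.
- The Predictors section fixes comorbidities at the index date, when earlier RRT has already been excluded. The dynamic predictors it names are laboratory tests and medication status. A time-updated dialysis indicator would inform the model but leave the outcome treatment-driven, and transplant would still be uncovered.
- Because t0 can follow the index date, a patient who starts RRT in that gap is eligible and enters with a post-RRT baseline.

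Nothing shown closes the gap.

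**2. How small a rise meets WRF at high creatinine?** The inputs are the two thresholds in Outcomes. The absolute criterion is the easier one above 26.5 / 0.30 = 88.3 µmol/L. As a share of the starting value it is:

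| Starting creatinine (µmol/L) | 26.5 as a relative rise |
|---|---|
| 300 | 8.8% |
| 400 | 6.6% |
| 600 | 4.4% |
| 800 | 3.3% |

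A modest swing in a patient on dialysis can therefore meet WRF without any change in native function.

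**3. What could the size be?** The outcome prevalence of about 25% comes from the Sample size section. Everything else is assumed: a share r of 0.2% to 2% of prediction windows after RRT start, a fraction q of 50% to 90% of those windows meeting WRF, and a typical error e of 100 to 200 µmol/L in them against b = 20 elsewhere.

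*WRF prevalence* = (1 − r) × 0.25 + r × q

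- Low: 0.998 × 0.25 + 0.002 × 0.5 = 0.2505. RRT windows supply 0.001 / 0.2505 = 0.4% of events.
- High: 0.98 × 0.25 + 0.02 × 0.9 = 0.263. RRT windows supply 0.018 / 0.263 = 6.8% of events.
- If instead no post-RRT window met WRF (q = 0, r = 2%), prevalence would fall to 0.98 × 0.25 = 24.5%.

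*RMSPE* = √[(1 − r) × b² + r × e²]

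- Low (r = 0.2%, e = 100): √(399.2 + 20) = 20.5. RRT windows supply 20 / 419.2 = 4.8% of squared error.
- High (r = 2%, e = 200): √(392 + 800) = 34.5. RRT windows supply 800 / 1192 = 67% of squared error.
- With b = 30 the same corners give 30.3 and 41.0.
- With e = 50 the effect nearly vanishes: at r = 0.2%, √(399.2 + 5) = 20.1; at r = 1%, √(396 + 25) = 20.5.

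**The case against.** The best reply is that the harm is assumed rather than shown, and much of that stands. The article gives neither an RRT rate nor a post-RRT error. A high creatinine level is not the same as a large prediction error: the models use each patient's history up to the time of prediction, so a persistently high series is partly anticipated and the largest errors should sit at transitions. The neural network log-transforms creatinine, which damps outlying values. Supplementary File S2, which is not shown, gives acceptable ranges for predictors. Baseline covariates are moved to t0 when it falls later, so dialysis started in the gap might be visible to the model. None of this replaces a rule for when the series ends.

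A reader might also draw four stronger conclusions that the document does not support.

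- **That the WRF endpoint is corrupted.** Under the assumed range its prevalence moves by little more than one percentage point.
- **That RMSPE decides which model is chosen, so the choice would be wrong.** The Model selection section describes a consensus exercise in which accuracy is one of several criteria, and the plan also assesses calibration, discrimination and net benefit. All three models face the same records. The statistical models use clinical scales while the network uses transformed values, so extreme records may affect them unequally, but no change in ranking has been shown.
- **That the worst renal outcomes are lost.** A patient declining towards RRT can meet WRF beforehand, and hospitalization for AKI is a secondary outcome. Only values after RRT start are affected.
- **That the plan itself concedes creatinine is uninterpretable under RRT.** The article gives no reason for the exclusion.

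**Conclusion.** The concern holds as a gap in the analysis rules. Followed as written, the plan fits and scores treatment-driven creatinine as native renal function, and for RRT between diagnosis and t0 it does so from the baseline onwards. This rests on the text alone.

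The size depends on assumptions. For 0.2% to 2% of windows with error 100 to 200 µmol/L against 20, RMSPE goes from 20 to about 20.5 to 34.5, which is anything from negligible to material. WRF prevalence goes from 25% to at most about 26.3%. The exposure lies mainly in model fitting and the RMSPE accuracy criterion, and much less in the frequency of the primary endpoint. The rule should be settled before the models are developed; the gap does not invalidate the design.

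**What to change.** 1. In Participants, apply the exclusion to any RRT before t0, so that no baseline is a post-RRT value.
2. In Participants and Outcomes, end the modelled creatinine series and the WRF assessment at the start of RRT.
3. In Outcomes and Statistical modelling, state how RRT start counts: as a component of WRF or as a competing event in the joint model. It should not be treated as non-informative censoring, because it is closely tied to the outcome. Which of the two to use is for the study team to decide.
4. State a rule for temporary RRT. The exclusion's definition includes dialysis and filtration, so taking the first code as final would end follow-up in patients who later recover.

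Whether dialysis stays a code-list factor need not be settled here; its codes are needed to apply the exclusion in any case.

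The cost is a few lines of text and little extra coding, since the plan already defines RRT for the exclusion and lists dialysis in Table 1. A small number of later records is lost, including recovery after temporary RRT if follow-up ends there. If RRT start becomes a WRF component, the primary endpoint changes and that should be declared. Reporting the number of patients who start RRT after diagnosis, and RMSPE with and without their later records, would replace the assumed sizes with observed ones.
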